## Methods and analysis

### Study design

The study is a two-arm, parallel-group, multicentre randomised controlled superiority trial designed to evaluate the effectiveness of a wearable-controlled serious game played on a smartphone or a tablet for distal radius fracture rehabilitation. Patients are randomised in a 1:1 ratio.

### Participants and setting

Consecutive patients aged 18 years or older, with any type of conservatively or operatively treated closed distal radius fracture, are eligible to participate in the study. Table 1 provides a complete overview of inclusion and exclusion criteria. Patients are recruited from four different teaching hospitals in the country, of which one is an academic centre. Patients are recruited at the outpatient clinics, where clinicians will be approached for permission to contact their patients about the study. Before starting trial participation, written informed consent will be obtained from all participants by the research staff.

**Table 1 T1:** Inclusion and exclusion criteria

Inclusion criteria	Exclusion criteria
1. Any type of closed distal radius fracture with no injury to the skin of the affected limb	1. Polytraumatised patients (Injury Severity Score ≥16)
2. Good position after reposition or operative fixation, defined by <10° of inclination in any direction, <5 mm shortening of the radius compared with the ulna, <2 mm disposition of intra-articular fragments	2. Bilateral wrist fractures or other concomitant injuries to the affected limb
3. Fracture primarily treated with conservative (cast) immobilisation or operative fixation (ORIF)	3. Patients with other disease or injury causing a clinically relevant loss of function or range of motion in the wrist, as reported by patients (including Parkinson’s disease, having had a cerebral vascular accident, amyotrophic lateral sclerosis, neuropathy of any kind)
4. Fracture considered to be consolidated by treating physician (trauma or orthopaedic surgeon or surgical resident in training)	4. Previous fractures or any condition affecting the injured wrist with clinically relevant residual pain, loss of function or range of motion
5. Possible to start rehabilitation exercises within 5 days after cast removal or operative fixation, as decided by treating physician (trauma or orthopaedic surgeon or surgical resident in training)	5. Any medical contraindication to start rehabilitation within 5 days after operation or cast removal, including dislocation of the fracture, tendon rupture or complex regional pain syndrome, as decided by the treating specialist
6. Age ≥18 years	6. Insufficient proficiency of Dutch or English in speech and written language, or inability to complete the Dutch questionnaires
7. Written informed consent	7. Not in the possession of, or able to obtain for the duration of our study, a smartphone or tablet compatible with the serious game
	8. Visual impairment preventing use of the smartphone-based game

ORIF, open reduction internal fixation.

Patients with a medical history of loss of function due to injury or illness in either hand or wrist, polytraumatised patients, as well as patients who suffered bilateral wrist fractures or other injuries to the affected limb, are excluded. Patients who are not in the possession of a smartphone or tablet compatible with the serious game, as well as patients with a visual or mental impairment preventing the proper use of smartphone or tablet, are excluded. Those unable to understand spoken or written Dutch or English will be unable to complete the questionnaires and are therefore not eligible for participation.

### Randomisation

When patients have been found eligible, and after they signed the informed consent form, baseline measurements are obtained. After baseline measurements, the local researcher contacts the central research coordinator for randomisation to take place and to receive information on group allocation. Randomisation sequence is determined by an independent researcher using an online automatically generated randomisation list (via www.sealedenvelope.com). Allocation concealment is obtained using sealed opaque envelopes. Patients are randomised using block randomisation in blocks of four, stratified for age (18–64, and 65 years or above) and for treatment type (conservative treatment using immobilisation or operative treatment by means of internal fixation) to ensure a balanced randomisation into the two groups.

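### The single disclosed block size of four lets anyone who sees a whole stratum's sequence, on the documents only the central coordinator, know a third of allocations in advance; varying it is a cheap improvement with a small gain

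*Protocol article*

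**What the plan says.** The Randomisation section of the protocol article fixes the scheme: "Patients are randomised using block randomisation in blocks of four, stratified for age". The age groups divide at 65, and the second factor is whether the fracture was managed conservatively or by surgery. Two age groups by two treatment types make four strata. Centre is not named as a factor. The Study design section gives the ratio: "Patients are randomised in a 1:1 ratio". Each block therefore holds two patients per arm.

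An independent researcher produces the list, and sealed opaque envelopes conceal it. Once eligibility, consent and baseline measurements are complete, "the local researcher contacts the central research coordinator for randomisation to take place and to receive information on group allocation".

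Under Participants and setting, "Patients are recruited from four different teaching hospitals in the country, of which one is an academic centre". Recruitment is described as consecutive, but it involves judgement: "clinicians will be approached for permission to contact their patients about the study", and inclusion criterion 4 in Table 1 reads "Fracture considered to be consolidated by treating physician".

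The article does not call the trial open-label. Even so, a sensor-controlled game against exercises on paper cannot be hidden from patients, and the Gameplay section has the clinician encourage patients to keep using the game. The clinician who takes the measurements and the analysing statistician are blinded.

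**The concern.** An envelope conceals an assignment only if its content cannot be worked out. With a fixed block of two and two, the last assignment of every block follows from the first three, and sometimes the third follows from the first two. Someone who could work out the next arm and could also influence who enters, or when, could shift the type of patient between arms.

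Intention-to-treat analysis does not repair selection that happens before randomisation. Stratification balances only age group and treatment type. The primary outcome, the PRWE, is completed by patients who know their arm, so the blinded measurer and statistician do not protect it. That leaves allocation concealment as one of the main safeguards.

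**Working it through.** The plan gives no predictability figure, so there is none to reproduce. The inputs are block size 4 and four strata (Randomisation), the 1:1 ratio (Study design), and four hospitals (Participants and setting). Hospital shares of a stratum are not given and are assumed below.

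**1. Observer who sees the whole stratum, fixed blocks of four.** A 2+2 block has six equally likely orders.
- AABB and BBAA: positions 3 and 4 are certain (2 each).
- The other four orders: only position 4 is certain (1 each).
- Certain allocations per block: (2 × 2 + 4 × 1)/6 = 1.333. Share: 1.333/4 = 33.3%.

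Best-guess accuracy by position is 1/2, 2/3, 2/3 and 1. For position 3, the first two match with probability 1/3 (guess certain) and differ with probability 2/3 (guess even): 1/3 × 1 + 2/3 × 1/2 = 2/3. The mean is (0.500 + 0.667 + 0.667 + 1)/4 = 70.8%.

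One third is exact for complete blocks. If the 92 patients fell evenly into the strata (an assumption: 92/4 = 23 each, last block incomplete), the certain share would be about 30%.

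**2. Same observer, block sizes in random order.** This is a simulation of 24-patient strata. The observer knows the possible sizes but not where blocks end, and guesses optimally.

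| Blocks | Certain | Best guess correct |
|---|---|---|
| 4 fixed | 33% | 71% |
| 4 and 6 | about 6% | 68–69% |
| 4, 6 and 8 | 2–3% | 67% |

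**3. Staff at one hospital who see a share s of a stratum.** Suppose they know the block position. An assignment is certain to them only if both earlier patients who used up one arm were theirs, which has probability s². The certain share of their own allocations is then s²/3:
- s = 25%: 0.0625/3 = 2.1%
- s = 50%: 0.25/3 = 8.3%
- s = 70%: 0.49/3 = 16.3%

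Stratum sequences are not split by centre, so local staff would not normally know the block position. Without it, essentially nothing is certain. If they simply guess the arm that is behind in their own running count, simulation of fixed blocks gives about 53% correct at s = 25% and 56% at s = 50%, against 50% by chance. With blocks of 4 and 6 the figures are practically the same.

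**4. Who has which view.**
- *Central coordinator:* every local researcher obtains allocations from this role, so it can see whole strata. No section gives it a part in choosing patients.
- *Local researchers:* they receive the allocations of their own site.
- *Treating clinicians:* they give permission for contact and judge consolidation and readiness to start. No section shows them the allocations of other hospitals.

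**The case against.** A reader might infer that the clinicians whose judgement governs entry can foresee one third of the assignments. The documents do not support that. The one third belongs to whoever sees a whole stratum, the discretion belongs to treating clinicians, and the article keeps the two apart: independent generation, central release, and release only after consent and baseline. This part of the objection stands, and it limits the size of the point.

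It also stands that the proposed change does almost nothing for local staff, and that for a full-stratum observer it removes certainty much more than it reduces good guessing. Consecutive recruitment limits picking in principle. Analysing change from baseline, with baseline measured before allocation, partly absorbs selection on the initial wrist score. A block size printed in an article does not prove that recruiting staff knew it while enrolling. The scheme contains no misstatement or contradiction, and the sample size is not affected.

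The objection does not remove the design weakness itself. Envelopes and central release do not stop deduction by the person who handles every release. The article does not say that the coordinator has no contact with recruitment, and the word consecutive does not take away the judgements in Table 1.

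**Conclusion.** The point holds as a modest weakness. One fixed, disclosed block size makes 33% of allocations certain, with 71% guessed correctly, for an observer of a full stratum. On the documents that is only the central coordinator. For staff at one hospital the realistic figure is about 53% to 56% correct guesses, assuming they see 25% to 50% of a stratum.

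The risk becomes material mainly if the coordinator also recruits, if the coordinator tells sites what comes next, or if one hospital fills most of a stratum. The article settles none of these. That patients and treating clinicians know the arm is inferred from the nature of the interventions. There is no ground to say that selection has occurred or that the primary comparison is biased. This is a cheap improvement, not an error that must be corrected.

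**What to change.** For any allocations not yet issued, have the independent researcher generate a new list with block sizes of 4 and 6 (or 4, 6 and 8) in random order. Keep the sizes from the coordinator and recruiting staff until recruitment closes. The strata, the 1:1 ratio and the sample size stay as they are.

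The cost is a regenerated list, new envelopes and a short amendment. The largest possible imbalance within a stratum is half the largest block, so it rises from 4/2 = 2 to 6/2 = 3 (or 8/2 = 4). The article does not say how many allocations remain. If none do, the change has no effect, and it would be enough to state in the report whether the coordinator took part in recruitment and how many patients each hospital contributed to each stratum.

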### Interventions

After randomisation, patients start participation in the trial as soon as their fracture has been qualified as stable or consolidated, and patients are fit to start active exercises as determined by the clinician; this is either directly, or as soon as possible, but within 3–5 days after cast removal or successful operative fixation. Together with specialised hand and wrist physiotherapists and exercise therapists, a standardised protocol for the first 6 weeks—when most progress is to be expected—has been established that is both embedded within the game and explained to patients.^38^ All patients are instructed by their clinician to perform the hand and wrist rehabilitation exercises three to five times per day. In addition, patients receive a simple diary to complete, with instructions to register their frequency and duration of exercises daily, as well as any physical complaints they may have during exercising.

#### Intervention group

Patients who are randomised to the game group receive a download link via email, together with instructions on how to download and install the game on their own smartphone or tablet (iPad or iPhone, Apple, Cupertino, California, USA). Patients are instructed to strap one motion sensor to the dorsum of the hand and to strap a second one to the proximal forearm (figure 1). If patients are only in the possession of a compatible smartphone, they will receive the Myo gesture control armband (Thalmic Labs, Kitchener, Ontario, Canada). This sensor is worn around the hand, in combination with the patient’s own smartphone strapped around the forearm with the screen upwards and still visible (figure 1). If patients are only in the possession of a compatible tablet, or if they prefer this option over using their smartphone, they receive two Valedo sensors (Hocoma AG, Zurich, Switzerland). Two separate sensors are used since the tablet cannot be strapped to the arm to be used as a motion sensor. Both types of sensors control the exact same game in the same manner, the motions are the same, and gameplay in both types of game controller has been validated extensively, as described previously.^38^ Both types of motion sensors are CE-marked, have been found fit to act as a game controller and are able to monitor wrist ROM. The sensors are connected to the smartphone via Bluetooth. By using two separate motion sensors placed proximally and distally of the wrist joint, isolated wrist motions are used for game control and patients cannot ‘cheat’ by moving the shoulder joint or the fingers. All otherwise necessary instructions are embedded within the game, making the game ‘self-explanatory’. Intervention group patients will practise with the game for 6 weeks, after which they return the motion sensor to the hospital and are encouraged to continue exercising independently.

**Figure 1 F1:**
[figure not shown]
Sensor placement. (A) iPhone and Myo; (B) two Valedo sensors.

#### Gameplay

The *ReValidate!* game shows an underwater world in which the patient plays one level consisting of three different mini-games of similar difficulty (online supplemental video). Each mini-game has its own avatar, and is controlled by one specific wrist motion: the ‘anglerfish’ mini-game is controlled by pronation and supination, the ‘shark’ mini-game is controlled by palmar and dorsal flexion of the wrist, and the ‘penguin’ mini-game is controlled by radial and ulnar deviation (figure 2). The patient plays one level three to five times per day, for a duration of approximately 10–15 min. Every playing session starts with a ‘warm-up’ of the motions, during which the motion sensors are calibrated and the game is set to the patients’ own maximum ROM. This ensures the game remains challenging yet playable, and prevents overstraining the wrist to make movements outside of the patients’ own ROM. A new level is unlocked each day, provided that at least one playing session has been completed that day, so the game remains motivating and challenging. All levels consist of an underwater parkour that needs to be completed, only the surroundings and route change. Levels gradually increase in length and difficulty over the course of 6 weeks, in the same manner as a physiotherapy treatment programme increases in intensity over time. Patients are motivated by a daily ‘push notification’ reminder to exercise, and by optional high score rankings. Bonus points can be gathered by playing consistently three to five times per day and by obtaining ‘collectibles’ found in the different levels. The game application registers frequency and duration of gameplay and records progress in terms of ROM in degrees.

10.1136/bmjopen-2020-042629.supp1Supplementary video

**Figure 2 F2:**
[figure not shown]
Different avatars are used in the game. (A) The anglerfish is controlled by pronation and supination; (B) the shark is controlled by palmar and dorsal flexion; (C) the penguin is controlled by radial and ulnar deviation.

Because the swimming motions of the fish are comparable with the wrist motions needed to control the mini-games, gameplay through the embedded wrist exercises is intuitive and natural.

The game has been designed specifically for wrist rehabilitation by a company specialised in the development of rehabilitation games. An iterative design process was set up to ensure embedding of the standard exercise protocols. The game has been tested at all stages of development by experts and novices, including trauma surgeons, specialised hand and wrist surgeons, occupational therapists and physiotherapists, as well as by end-users.^38^ Content has been checked for validity and exercise completeness both by user groups of patients and medical experts, and was found to be similar to regular physiotherapy exercise regimens.^38^ Should patients encounter any problems with the game, they are provided contact details of a study coordinator. For any medical questions or concerns, patients are referred back to their treating specialist. Though not preferred, patients receive a referral for additional physiotherapy upon request. They will be motivated by their clinician to continue practising using the game. The number of physiotherapy visits will be registered prospectively.

#### Control group

Patients in the control group receive standard care, consisting of home-based unsupervised wrist exercises, and upon request or recommendation by their clinician, a referral for specialised hand physiotherapy or occupational therapy. An overview of simple exercises for the three main motions in the wrist (palmar/dorsal flexion, pronation/supination and radial/ulnar deviation) is provided on paper, together with an explanation of exercises by the clinician. Patients are instructed to perform controlled movements up to a point that cause a stretch but no pain. Patients are instructed to practise these movements three to five times daily, approximately 10–15 min per session. This regimen has been developed in cooperation with specialised hand and wrist physiotherapists and occupational therapists, and is most reflective of current standard practice. All patients referred to physiotherapy are instructed to perform active exercises without load. The number of physiotherapy visits will be registered prospectively.

### Outcome measurements

Standard demographic information including age, sex, fracture type according to the Arbeitsgemeinschaft für Osteosynthesefragen/Orthopaedic Trauma Association fracture classification,^39^ and the type of treatment is obtained directly after inclusion. Follow-up visits take place at 2, 6, and 12 weeks postoperatively or after cast removal, for operatively or conservatively treated patients, respectively. A timeline of the trial is shown in figure 3. The primary outcome measure, which is the validated Patient-Rated Wrist Evaluation (PRWE) questionnaire is completed by patients at all follow-up visits.^40 41^ The active ROM is measured in degrees using an analogue universal goniometer. ROM and grip strength are measured in both hands, where grip strength is measured in kilograms, using an analogue hand dynamometer (Baseline, Fabrication Enterprises, White Plains, New York, USA). The maximum value of two measurements with 5 min rest in between is used for analysis. All measurements are performed by a clinician blinded to group allocation that has been specifically trained for this trial, and is experienced in taking ROM and strength measurements in daily practice.

**Figure 3 F3:**
[figure not shown]
Schematic timeline of the study showing the randomisation and follow-up planning, as well as the outcomes measured during each visit. ORIF, open reduction internal fixation; PRWE, Patient-Rated Wrist Evaluation; ROM, range of motion.

Patients in both study arms complete a questionnaire, that was specifically developed for this trial, on their self-efficacy, experiences and perceived effectiveness of their exercise programme. Pain scores on a Visual Analogue Scale are recorded, and patients are asked about the frequency, if any, of visits to a physiotherapist or occupational therapist. In addition, partial or complete return to work, or to normal functioning if patients were currently unemployed, is registered. Patients are reminded by the researcher to fill out their exercise diary at every follow-up visit and are asked to return their completed exercise diary at 6 weeks of follow-up. In the intervention group, the data on exercise frequency and duration, as well as ROM, will also be retrieved from the serious game. The frequency reported by patients in this group will be compared with the data from the game application, which stores all exercise data including frequency, duration and the ROM measured.

### Sample size calculation

The primary outcome is the PRWE questionnaire outcome score after 6 weeks of treatment. This questionnaire has been validated previously,^40^ and has a minimal clinically important difference of 11.5, with 1.5 for the pain subscale and 10 for the function subscale.^41^

An elaborate and important Cochrane review on the effect of physiotherapy after distal radius fractures reports only three studies comparing a regular physiotherapy regimen with an unsupervised home-exercise programme.^15^ These comparisons are relevant here, since the use of this serious game can be compared with an unsupervised home-exercise programme. Only one of these three trials reports patient-rated functional outcomes in addition to ROM or grip strength values.^18^ This study looks into the effects of a progressive home-exercise programme, compared with the effect of 12 physiotherapy sessions over a 6-week period in patients with an operatively treated distal radius fracture. They found a positive effect in favour of the home-exercise programme, with PRWE scores of 18.5 (SD 15.9) for the home-exercise group, compared with 36.1 (SD 13.9) in the physiotherapy group after 6 weeks.^18^

As a result, using the SD of 15.9, for a two-sided t-test in two groups with an alpha of 0.05, a power of 90% (1–beta=0.9), an allocation ratio of 1:1, this leads to necessary group sizes of 42 patients per group to detect a clinically relevant difference of 11.5 points at 6 weeks. With a 10% dropout rate, a total of 92 patients are needed for this trial.

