**Methods and analysis:**

To test the effectiveness of a mobile serious game for distal radius fracture rehabilitation compared with standard care, a multicentre, randomised controlled clinical trial was designed. Primary outcome will be the Patient-Rated Wrist Evaluation (PRWE) score after 6 weeks of treatment. Secondary outcomes are range of motion, grip strength, pain scores, and self-reported treatment adherence after 2, 6 and 12 weeks of treatment.

Adult patients with any type of closed distal radius fracture are included directly after non-operative or operative fracture treatment. Patients are recruited in the outpatient clinics of four teaching hospitals. The intended sample size is 92 patients, based on the minimal clinically important difference of the PRWE score at 6 weeks, using a superiority model.

Patients are randomised between using the wearable-controlled mobile serious game *ReValidate!* (intervention group) and standard care consisting of unsupervised exercises and a referral for physiotherapy or exercise therapy upon request or recommendation by the treating clinician (control group).

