**Trial registration number:**

Dutch Trial Registry (NTR), NL6140, protocol V.2.

Strengths and limitations of this studyThis study is a randomised controlled trial comparing a wearable-controlled mobile serious game for wrist rehabilitation with standard care, the first of its kind, to the authors’ knowledge.The study is sufficiently powered to show a clinically important difference in the outcome measurements of the primary endpoint.By measuring treatment adherence, both subjectively and objectively, a reliable comparison between patient-reported and objectively monitored treatment adherence can be made.The control group receives an accurate representation of the current standard of care.The analysing statistician will be blinded to randomisation group.

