### Data analysis

The primary outcome is the PRWE score at 6 weeks. This outcome is represented as the change in outcome scores from T0 to T2 (delta, T2–T0). An intention-to-treat analysis is performed, and any missing data are imputed. Data will be analysed using a two-sided t-test or the Mann-Whitney U test, depending on normality of the distribution.

For the secondary continuous outcomes (PRWE score at 2 and 12 weeks, ROM, grip strength, pain scores), a repeated measures analysis of variance will be performed, where group assignment (game group vs control group) is the between-subjects factor, and time of visit (baseline, 2, 6 or 12 weeks follow-up) is the within-subjects factor. In case of a non-normal distribution, generalised estimating equations will be used. An intention-to-treat analysis will be performed, and any missing data will be imputed using multiple imputation. Other (secondary) functional outcomes are analysed as a percentage of the unaffected wrist. Bonferroni correction is applied to all secondary outcomes to correct for multiple tests. Therefore, p values of <0.0045 will be considered statistically significant.

Baseline data and secondary outcomes include categorical data such as fracture type and treatment type. These data will be analysed using the Χ^2^ test, and outcomes will be presented as the differences in frequencies. P values of <0.05 are considered statistically significant. Treatment adherence is measured using a self-reported diary. The number of exercise sessions and the total duration of exercising are continuous variables that will undergo quantitative and qualitative synthesis using a two-sided t-test or a Mann-Whitney U test as appropriate.

The diaries that are handed in after the trial period are analysed for the percentage of days the diary is completed and the total estimated time of exercising. In the intervention group, these data are also compared with the total time of exercising as registered within the game. In addition, should not all diaries be completed, the number of diaries handed in after the study period is registered. These data are then analysed using the Χ^2^ test, and outcomes will be presented as the difference in frequencies.

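### The 90% power rests on the SD of the 6-week PRWE score, but the planned primary test is an unadjusted comparison of change from baseline, so the stated power is unsupported for that test

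*Protocol article*

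**What the plan says.** The abstract (Methods and analysis) fixes the endpoint as a score at one time point: "Primary outcome will be the Patient-Rated Wrist Evaluation (PRWE) score after 6 weeks of treatment". The Sample size calculation section uses the same definition. It reports 6-week PRWE results from a cited trial, 18.5 (SD 15.9) with home exercise and 36.1 (SD 13.9) with physiotherapy, and takes the first SD: "using the SD of 15.9, for a two-sided t-test in two groups with an alpha of 0.05, a power of 90" per cent. Allocation is 1:1 and the aim is "to detect a clinically relevant difference of 11.5 points at 6 weeks". The result is 42 per group, and 92 in total after a 10% allowance for dropout.

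The Data analysis section first repeats that the primary outcome is the 6-week score, then adds: "This outcome is represented as the change in outcome scores from T0 to T2". That difference is compared by a two-sided t-test or, if not normally distributed, a Mann-Whitney U test. No baseline covariate is named for the primary analysis.

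The strengths and limitations list states: "The study is sufficiently powered to show a clinically important difference in the outcome measurements of the primary endpoint".

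**The concern.** A score at 6 weeks and a change from baseline to 6 weeks are different variables with different variances. The trial is sized on the first and analysed on the second. Nothing in the article presents 15.9 as an SD of change, and no SD of change, baseline SD or correlation is given from which one could be derived.

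Two things are at stake. First, the stated 90% power, and the strengths claim built on it, are not shown to hold for the confirmatory test. Depending on the missing values, the unadjusted change score can be less precise than a comparison that ignores baseline altogether. Second, the article carries two descriptions of the primary variable. Unless one is removed, the choice between them could be made after the data are seen.

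**Working it through.** **Inputs from the Sample size calculation section:** two-sided alpha 0.05, power 90%, allocation 1:1, difference 11.5, SD 15.9 (cross-sectional, 6 weeks), 42 per group.

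**Input from the Data analysis section:** the variable tested is T2–T0. T0 and T2 are not defined in the text available (the timeline figure is not shown). I read them as baseline and 6 weeks, which fits the wording of that section and the visits at 2, 6 and 12 weeks.

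**Not in the article, so assumed:** baseline SD (SD0) of 12, 15.9 or 20; rho from 0 to 0.6.

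**Step 1. Reproduce the plan's figure.** The standardised difference is 11.5/15.9 = 0.723. With the exact noncentral t distribution, 41 per group gives 89.9% power and 42 gives 90.6%. The stated 42 is therefore correct for a t-test on 6-week scores.

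**Step 2. SD of the variable actually tested.**

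SD(change) = sqrt(SD0² + SD6² − 2 × rho × SD0 × SD6)

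Setting this equal to SD6 gives the break-even condition rho = SD0/(2 × SD6):
- SD0 = 12: 12/31.8 = 0.38
- SD0 = 15.9: 15.9/31.8 = 0.50
- SD0 = 20: 20/31.8 = 0.63

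Below the break-even rho the change score is noisier than the plan assumes; above it, less noisy.

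**Step 3. Power of the planned t-test on change.** Difference 11.5, 42 per group, SD 15.9 at both times, so SD(change) = 15.9 × sqrt(2(1 − rho)):

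| rho | SD of change | Power | n per group for 90% |
|---|---|---|---|
| 0 | 22.5 | 64% | 82 |
| 0.2 | 20.1 | 74% | 66 |
| 0.3 | 18.8 | 79% | 58 |
| 0.4 | 17.4 | 85% | 50 |
| 0.5 | 15.9 | 90.6% | 42 |
| 0.6 | 14.2 | 96% | 34 |

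The assumed baseline SD moves these figures in both directions. At rho 0.4, power is 91.5% with SD0 = 12, 85% with SD0 = 15.9 and 74% with SD0 = 20.

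**Step 4. Baseline-adjusted analysis of the 6-week score.** The residual SD is 15.9 × sqrt(1 − rho²), which cannot exceed 15.9. At 42 per group, power is 90.6% at rho 0, 92% at 0.2, 93% at 0.3, 95% at 0.4 and 97% at 0.5. The degree of freedom spent on the covariate does not change these rounded figures. The baseline SD does not enter.

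**The case against.** The strongest reply is that nothing here shows power has been lost. With equal SDs and rho above 0.5, the planned test exceeds its stated 90%. That is right. A reader might infer that the trial is underpowered, but the article gives no value of rho from which to conclude this. It is tempting to add that baseline scores taken soon after surgery or cast removal must correlate weakly with 6-week scores. No data in the article support that, and I do not rely on it.

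A second reply is that 0.5 is not a general threshold. This also stands: it holds only when the two SDs are equal, which is why the general condition is given above.

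Third, the plan has some slack, because it uses the larger of the two published SDs. The pooled value is sqrt((15.9² + 13.9²)/2) = 14.9. With that SD at both times, the change score reaches 90% power at rho of about 0.43, and gives 84% at 0.3 and 89% at 0.4. The dependence on rho is softened but not removed.

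Fourth, validity is not in question. Under randomisation the difference in mean change and the difference in mean 6-week score have the same expectation, so the 11.5-point target stays relevant and the t-test on change is unbiased with the correct type I error. A reader might infer bias from chance baseline imbalance. Such imbalance does carry into an unadjusted change score through regression to the mean, but this is an argument about precision given the observed baseline. It does not show the method to be wrong.

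What survives these replies is the mismatch: the SD belongs to one variable and the test is applied to another.

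**Conclusion.** The concern holds as a gap in justification at the primary endpoint. The stated 90% power, and the claim of sufficient power in the strengths list, are unsupported for the analysis described. Over rho from 0 to 0.6, with SD 15.9 at both times and 42 evaluable per group, power of the planned t-test runs from 64% to 96%. The break-even rho is about 0.38, 0.50 or 0.63 for a baseline SD of 12, 15.9 or 20. The baseline SDs and correlations are my assumptions; the difference, 6-week SD, alpha and group size are the plan's own. The documents do not establish that the trial is underpowered or that its estimate would be biased.

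**What to change.** Name one primary endpoint, the PRWE score at 6 weeks, in every section. Analyse it by ANCOVA (linear regression) on treatment group with baseline PRWE as covariate, ideally adding the two stratification factors, age group and treatment type. Report the adjusted mean difference with its 95% confidence interval against 11.5 points. Remove the unadjusted change-score test, and settle this before outcome data by group are examined.

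Power is then about 90% or more whatever the value of rho, on two conditions:
- The 6-week SD is 15.9. It comes from operatively treated patients only, whereas this trial also enrols conservatively treated ones. ANCOVA does not protect the power if the true SD is larger.
- 42 per group are evaluable. Losing 10% of 92 leaves 82.8, or about 41 per group, where power on the 6-week score is 89.9% at rho 0.

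If the change score is kept instead, justify an SD of change and restate the power and, if needed, the sample size.

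The first option costs only wording. A T2–T0 score already requires a baseline PRWE, so no new data and no extra patients are needed. That baseline PRWE is collected before randomisation is inferred from the randomisation and analysis sections, and should be stated outright.
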